##### Monitoring

A data audit will take place at least once a month to ensure all forms are completed accurately. Depending on the recruitment rate, the data audit may take place more frequently. In terms of safety monitoring, all adverse events will be classified as either an adverse (AE) or a serious adverse event (SAE). These events may occur during screening and baseline data collection, or they may occur during the administration of the intervention. An adverse event may or may not be related to the data collection or intervention procedures. When an adverse event is identified, study personnel identifying the adverse event will report it to the study co-ordinator and the principal investigator. The study co-ordinator will then contact the participant and an electronic Adverse Event Report Form will be submitted to the research ethics board will be completed within 7 days of the event and within 48 hours for serious adverse events. Decisions to discontinue or modify the intervention for a participant will be on a case-by-case basis by the research team.

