#### Study Conditions

##### Intervention Condition – Fitbit +Behavioral Counselling

The intervention aims to increase daily step counts by ≥3000 steps per day from baseline. The intervention is comprised of five phases which will be delivered through six behavioral counselling sessions (four individual sessions, two group-based webinars). Participants will be provided with a SB workbook and Fitbit Inspire 2 (Fitbit LLC; San Francisco, CA) as an intervention tool to complement the behavioral counselling sessions. The Fitbit Inspire 2 displays steps, distance, calories, sleep/rest time, and provides reminders to move. The Fitbit app syncs wirelessly to computers and smart devices. PCS will be encouraged to wear the device continuously throughout the 12 weeks and to access their SB and activity data at least weekly via the application.

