#### Active Comparison Condition: Fitbit-only Control

Participants will receive a Fitbit Inspire 2, the Canadian 24-hour Movement Guidelines [34], and a list of free public health resources about maintaining a healthy lifestyle (e.g., Canada’s ParticipACTION app). Following a brief orientation session on how to use the Fitbit and overview of the provided public health resources, the Fitbit-only comparator condition will not receive additional behavioral support from the movement specialists for the intervention period.

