### Data Collection

Data will be collected at baseline (T_1_), post-intervention (F_1_), and 6 months post-intervention (F_2_). Participants will complete an electronic questionnaire on REDCap (20 minutes) and will be mailed an activPAL inclinometer. PCS will meet with a movement specialist blinded to group allocation through videoconferencing (i.e., Zoom) to ensure proper fitting of the activPAL, and to complete the physical function test (30 minutes). Study personnel completing data collection will be blinded to group allocation. A summary of outcomes and data collection time points is shown in Table 2. Participants will receive a $60 honoraria for study completion ($20 for each completed assessment; T_1_, F_1_, F_2_).

**Table 2 Tab2:** Summary of outcome measures

Item	Instrument	Study Period				
		Enrollment	Baseline Assessment/ Allocation	Post-Allocation 12-week Intervention	Post-Intervention	6 months Post- Intervention
		T_0_	T_1_	T_2_	F_1_	F_2_
Eligibility Screen	N/A	X				
Informed Consent	N/A	X				
Allocation	N/A		X			
1. **Primary Outcomes**						
Objectively-measured Sedentary Behavior	ActivPAL		X		X	X
2. **Secondary Outcomes**						
Self-reported Domain-specific Sedentary Behavior	LASA Sedentary Behavior Questionnaire		X		X	X
Objectively-measured Physical Activity	ActivPAL		X		X	X
Self-reported Physical Activity	GLTEQ		X		X	X
Motivational Processes	Standard measures from the M-PAC (15 items)		X		X	X
Mental Health	HADS		X		X	X
Quality of Life	FACT-General, FACT-Fatigue, SF-12		X		X	X
Health and Disability	WHODAS 2.0		X		X	X
Physical Function	30-second chair stand		X		X	X
Internet & Technology Use	eHEALS		X			
Patient Satisfaction	30 items				X	
3. **Covariates**						
Sociodemographics	6 items		X			
Medical History	10 items		X			

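### Adverse-event recording relies on staff identifying events and does not name the 6-month follow-up, while scheduled contact differs by arm, so counts by arm may reflect contact as well as risk

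*Protocol article*

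**What the plan says.** The Monitoring section covers all adverse events, whether or not related to the study, and grades each as serious or not. On timing it says: "These events may occur during screening and baseline data collection, or they may occur during the administration of the intervention". On how an event enters the record it says: "When an adverse event is identified, study personnel identifying the adverse event will report it to the study co-ordinator and the principal investigator". The report form goes to the ethics board within 7 days, counted from the event, with 48 hours given for serious events.

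The Intervention Condition section and Table 1 give the intervention arm an orientation and six counselling sessions: four individual and two group. Of the control arm, the Active Comparison Condition section says that, after a brief orientation, "the Fitbit-only comparator condition will not receive additional behavioral support from the movement specialists for the intervention period".

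Study Design places F2 at 9 months from baseline. Under Data Collection, both arms complete the REDCap questionnaire and meet blinded staff by videoconference at T1, F1 and F2. Table 2 lists the measures taken at those visits and has no adverse-event item.

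**The concern.** Three things that the text does state fit together badly.

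- The only trigger described is that a member of staff identifies an event.
- Opportunities for staff to do so during the 12 weeks lie mostly in one arm. They arise with the movement specialists who deliver the counselling and therefore know the allocation.
- The periods named for adverse events leave out the months in which the article expects participants to maintain their changed behavior.

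If the text is followed as written, a fall or strain in an intervention participant may come up at the next session, within a week or two. The same event in a control participant has no scheduled occasion to surface until F1. After F1, neither arm has a scheduled contact until F2. Any tabulation of events by arm could then mix differences in risk with differences in ascertainment, and the record for the follow-up months could be thin in both arms.

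**Working it through.** The article gives no adverse-event rate, comparison or figure, so there is nothing of its own to reproduce. The check has three parts: a count of contacts, an illustration on stated assumptions, and a look at the deadline.

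**1. Scheduled contacts (Table 1, Study Conditions, Data Collection)**

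| | Intervention | Control |
|---|---|---|
| Orientation | 1 | 1 |
| Sessions (weeks 3, 5, 7, 9, 10, 11) | 6 | 0 |
| Total over the 12 weeks | 7 | 1 |
| Assessments T1, F1, F2 | 3 | 3 |
| Total to 9 months | 10 | 4 |

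The control arm has no scheduled contact from orientation to F1, roughly 12 weeks. Neither arm has any from F1 to F2. F1 falls at about 3 months and F2 at 9, so (9 − 3)/9 = 67% of follow-up lies in a period that the Monitoring section does not name.

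**2. Illustration of unequal detection**

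From the document: 60 per arm. Assumed, because the document gives no values: the same true risk in both arms (10%, 20% or 40%), detection of 90% in the intervention arm, and detection of 70% or 50% in the control arm.

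Expected recorded participants = 60 × risk × detection. At 20% risk this is 60 × 0.20 × 0.90 = 10.8 in the intervention arm, against 60 × 0.20 × 0.70 = 8.4 or 60 × 0.20 × 0.50 = 6.0 in the control arm.

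The chance of a nominally significant excess in the intervention arm is approximated by Φ[(d − 1.96·SE₀)/SE₁]. Here d is the difference in recorded proportions, SE₀ the pooled standard error and SE₁ the unpooled one. For 0.18 against 0.10: d = 0.08, SE₀ = √(2 × 0.14 × 0.86/60) = 0.0634, SE₁ = √((0.18 × 0.82 + 0.10 × 0.90)/60) = 0.0629, so Φ(−0.70) = 24%.

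| True risk, both arms | Recorded, intervention | Recorded, control (70% / 50% detection) | Chance of false excess |
|---|---|---|---|
| 10% | 5.4 | 4.2 / 3.0 | 6% / 14% |
| 20% | 10.8 | 8.4 / 6.0 | 9% / 24% |
| 40% | 21.6 | 16.8 / 12.0 | 15% / 50% |

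With equal detection the counts agree (10.8 and 10.8 at 20% risk), and the chance is 2.5% in this direction, or 5% two-sided. The approximation is rough at small counts.

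The apparent risk ratio is simply the ratio of detection rates: 0.90/0.70 = 1.3 or 0.90/0.50 = 1.8, at any true risk. The table therefore shows what unequal detection would do. It is not evidence of how unequal detection will be.

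**3. The deadline against the contact schedule**

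Suppose events are spread evenly over time and a participant does not volunteer them. Of events in the 84 days before F1, only those in the last 7 days, 7/84 = 8%, could be reported within 7 days of occurring if first learned of at F1. Over the roughly 182 days to F2 the share is 7/182 = 4%. As written, this already applies to controls before F1 and to both arms after it.

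**The case against.** The best case on the other side is that this is a condensed article. A manual of operations and an adverse-event report form are mentioned but not shown, and the way events are elicited is commonly left to such documents. Table 2 summarises outcome measures, so the lack of an adverse-event row does not prove that nobody asks. Safety is not among the objectives, and no between-arm test of events is planned. All of this stands, and the absence of an enquiry schedule would be weak ground on its own.

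Four stronger readings are tempting and are not supported:

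- **Recording stops when the intervention ends.** The timing sentence is descriptive and says only when events may occur. The section covers all adverse events and allows for events linked to data collection, which runs to F2. The status of the follow-up months is unclear; they are not excluded.
- **Controls are uncontacted.** They have an orientation and the same assessments, where events can come to light. What is withheld is behavioral support from the movement specialists. Two of the six intervention sessions are group webinars, a weaker setting for disclosing an event.
- **The intervention arm will show more events.** This is a risk, and its size rests on detection rates that the document does not give.
- **The trial's safety claim fails.** The Discussion remark on safe delivery looks ahead to delivery over the internet. It is not a hypothesis of the trial.

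It can also be said that unequal contact works against the intervention and so cannot falsely reassure. That holds for the comparison between arms, but not for events missed in both arms between F1 and F2.

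**Conclusion.** The point holds in a limited form. The article describes a passive trigger, names periods that leave out about two thirds of follow-up, and schedules 7 contacts against 1 over the 12 weeks. Adverse-event counts by arm may therefore reflect contact as well as risk, and events between F1 and F2 may be missed. The size cannot be derived from the document. On the assumptions shown, the false excess ranges from trivial (5.4 against 4.2 participants) to substantial (21.6 against 12.0).

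The conclusion assumes that no unshown procedure already asks both arms the same questions through F2. If one does, only the wording of the Monitoring section needs attention. No planned efficacy analysis is affected. This is a cheap improvement worth making, with medium confidence.

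**What to change.** 1. In the Monitoring section, state that adverse events are collected in both arms from screening through F2.
2. Add the same fixed-recall questions (for example falls, injuries, pain limiting activity and hospital visits since the last assessment) to the existing REDCap questionnaire at F1 and F2 in both arms.
3. Base any by-arm summary of events on those answers. List events volunteered in counselling sessions separately, so that they are still reported but do not enter the comparison.
4. Reconcile the 7-day limit, which runs from the event, with events first learned of at F1 or F2. The 48-hour limit for serious events needs the same check, since its starting point is not spelled out. How to resolve this is for the investigators and the ethics board.

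The cost is 1 to 2 minutes more per questionnaire at two assessments that already take place, one sentence in the Monitoring section, and more minor events to file. Recall over three and six months will lose some minor events, and participants know their allocation, so ascertainment will be more nearly equal but not perfect.

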## Discussion

Developing and testing distance-based interventions that replace SB with PA are warranted for several reasons. First, supervised PA has a positive impact on clinical outcomes such as QoL and reducing treatment-related toxicities in PCS [7, 69, 70]. However, access to such interventions may be limited by cost, geographic reach, availability of qualified PA professionals, and safe facilities given transmission concerns from the recent COVID-19 pandemic. Even when supervised PA programs are offered to cancer survivors at low cost, uptake and adherence may be low at intervention completion [14]. Second, health behaviors such as PA and SB are important in the self-management of cancer. Men with prostate cancer indicate that they are more likely to seek information on the internet [71]. Therefore, there is a need for evidence-based interventions that are easy to access, low-cost and scalable. This is particularly salient during the pandemic given that being physically active in public spaces presents risks for transmission in vulnerable populations such as cancer survivors [72]. Adapting usual methods of lifestyle program delivery to home-based programs for general well-being, mitigating treatment toxicities, and improving clinical outcomes are needed. One such intervention is digital health behaviour change. Digital interventions use technologies such as text messaging, e-mail, mobile applications, videoconferencing, social media, websites, and online patient portals. These technologies increase access to information, connecting patients with health services as an approach to remote delivery of behaviour change interventions. Such technologies have been used successfully in promoting PA participation and dietary behaviours in cancer survivors [72].

Given that cancer survivors may face several barriers to engaging in PA programs, there is a need to develop and assess the efficacy of interventions that employ distance-based approaches (e.g., characterized by limited face-to-face contact and/or supervision) [73]. Groen et al. [73] conducted a systematic review examining distance-based PA behavior change interventions for cancer survivors where the results show that intervention effects on PA were small and new approaches were needed. The current study will build on our successful pilot study by using a more robust clinical design and focusing on maintenance of behavior change in two important ways. A series of behavioral counselling sessions based on the M-PAC will be adapted throughout the trial that move beyond intention formation to focus on maintenance. This is noteworthy as theory-based interventions result in meaningful changes in behavior compared to atheoretical approaches in cancer survivors [74], including PCS [75]. Finally, our prior work was a single-group feasibility study, while this current study will examine the effects of the intervention on SB in a well-powered RCT. Overall, the current intervention will move from a feasibility to an efficacy trial, focus on maintenance grounded in theory (e.g., M-PAC), include sustainable wearables (e.g., Fitbit) that could be integrated within typical delivery models of cancer care.

Cancer survivorship is now recognized as an essential cancer care component, and greater efforts on maintaining QoL is needed. Cancer Care Ontario published specific follow-up care guidelines for PCS [76]. These guidelines aim to promote comprehensive follow-up care, optimal health, and QoL in PCS, which includes health promotion (i.e., PA) and management of physical and psychosocial side effects. Therefore, decreasing SED and increasing PA may be an effective health promotion strategy for PCS. The current intervention has high potential for broad reach and impact on both PCS and their support networks, as it can ultimately be delivered safely through internet- and mobile-based applications. With internet usage growing fastest among older Canadians [77], our study will create a unique distance-based platform that could be scaled for use by clinical and community-based organizations as a low-cost, supportive care tool to improve QoL for all cancer survivors across Canada.

## Data Availability

The datasets used and/or analysed during the current study are available from the corresponding author on reasonable request.

## Abbreviations

ACSM: American College of Sports Medicine
ADT: Androgen Deprivation Therapy
BMI: Body Mass Index
CSEP: Canadian Society of Exercise Physiologists
EWB: Emotional Well-being
eHEALS: eHealth Literacy Scale
FACT: Functional Assessment of Cancer Therapy
FWB: Functional Well-being
GLETQ: Godin Leisure-time Exercise Questionnaire
HADS: Hospital Anxiety and Depression Scale
LASA: Longitudinal Aging Study Amsterdam
LPA: Light Physical Activity
MVPA: Moderate-to-vigorous physical activity
M-PAC: Multi-Process Actional Control Approach
PA: Physical Activity
PAR-Q+: Physical Activity Readiness Questionnaire Plus
PASSS: Physical Activity and Social Support Scale
PCS: Prostate Cancer Survivors
PSQI: Pittsburgh Sleep Quality Index
PWB: Physical Well-being
RA: Research Assistant
REDCap: Research Electronic Data Capture
SB: Sedentary Behavior
SF-12: Short-form-12
SWB: Social Well-being
QoL: Quality of Life
WHODAS 2.0: World Health Organization Disability Assessment Schedule 2.0
